### Oversight and monitoring

The principal investigator DW and co-authors GC, IK, and CR coordinate the study at all study centres and meet monthly. The day-to-day management of the study will be performed by the steering committee with support from administrative staff from the standard healthcare system. The surgical methods in this trial have been used extensively at our clinic and are considered low-risk; thus, there is no need for a data monitoring committee. Neither the steering committee, authors, nor the sponsor has any competing interests. No external endpoint adjudication system will be used.

### Data handling

All data will be collected using the participants’ unique national identification numbers, then entered into REDCap by the assessor, and stored securely on servers provided by Lund University accessible only by the steering committee. Before interim analysis, and at the end of the trial, the steering committee will transfer collected data to a pseudonymous database using the unique participant ID provided at randomization to discriminate data. This database will be stored electronically behind firewalls provided by the sponsor. The only registry of the key to the participant ID and corresponding national identification number will be stored physically in a safe only accessible by the principal investigator.

## Discussion

Migration of K-wires may lead to reoperations following TBW fixation of olecranon fractures [48]. Using CF without K-wires eliminates the risk of migrating K-wires and retrospective studies have favoured this method [7, 16, 49]. Phadnis et al. advocate a similar method using non-metal sutures [50, 51], although reserving this technique for Mayo type 2a fractures. They reported a reoperation rate after suture fixation in 1 of 41 consecutive participants, though mixing fractures and osteotomies [8]. The same group runs an RCT which is currently recruiting participants [52]. A biomechanical cadaver study showed similar fixation strength following CF and TBW, theoretically rendering K-wires superfluous [53]. Based on these findings in retrospective and experimental settings, we designed the current RCT to provide level 1 evidence examining outcomes following CF vs. TBW. We have chosen not to include plate fixation as a comparator, as that method is not used for Mayo type 2a and 2b fractures at our clinic. Thus, including plate fixation would make the implementation of this study in our healthcare setting ethically difficult.

The planned study size is sufficient for detecting a clinically significant difference in the primary outcome, reoperation rates, if that difference is as big as in a retrospective study from our department [7]. We expect a high availability of participants for analysis. We do not expect missing data on reoperations due to participants moving out of the catchment area to differ from the previous retrospective study, on which the sample size calculation is based [16]. The retrospective study that underlies sample size calculations only included elderly subjects, which differs from the planned study. We believe that the reoperation rate in the planned RCT may be higher than in the retrospective study, as younger participants with high demands are more likely to require reoperations. However, it is also possible that K-wire migration will be less likely to occur in participants with better bone quality. Higher reoperation rates than assumed would yield higher statistical power to demonstrate a difference in reoperation rates.

The trial could be terminated early due to large differences in reoperations, complications, or *Quick*DASH scores between study groups, which would negatively affect statistical power for analyses of other outcomes. Early termination of the study will hamper its strength to draw conclusions on these outcomes, but we do not think it would be ethically justifiable to continue recruitment if the postulated exclusion criteria are met.

We believe this trial to be an ethically sound way of providing level 1 evidence comparing CF with TBW in Mayo type 2a and 2b fractures. It has the potential to influence the choice of treatment for these patients, thus improving patient outcomes and health.

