### Sample size

The primary outcome measure of the study is reoperation rates, and the sample size is based on this metric. Reoperation rates are assumed to be 13% for CF and 27% for TBW, based on a previous study at our institution [16]. As active patient participation is not required to calculate reoperation rates, and as it will be collected in the same health-care system as the previous retrospective study, we do not expect any drop-out of participants (relative to that study) for assessment of reoperations. The sample size of each arm needed to achieve 80% power is 98; thus, we plan to recruit a total of 200 participants, yielding 81% power.

We expect all 200 participants to be available for analyses of peri-operatively recorded variables (age, sex, fracture type, fluoroscopy DAP, fluoroscopy time and operation time). For analyses of complications, the same assumption is made as for reoperations, i.e. no drop-out relative to our previous retrospective study. For all other variables collected at follow-up, we expect 170 participants to be available for statistical analysis. The expected power for all variables at different sample sizes are shown in Table 1, including all relevant assumptions made.

**Table 1 Tab1:** Statistical power and sample size requirements for study outcomes

	**Power *****n***** = 200**	**Power *****n***** = 170**	***n***** needed for 80% power**	**MDD *****n***** = 100**	**MDD**	**MDD *****n***** = 170**	**MDD**	**x̄ or proportion**	**SD**	**MCID**

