### End of trial and early termination

Recruitment will end when 200 participants have been recruited.

Interim analyses will be performed by the data monitoring committee every 6 months, starting in May 2024. All participants that have completed the follow up at 6 weeks be included in the interim analyses. For ethical reasons, the recruitment will be terminated by the steering committee if any of the following criteria is met:A statistically significant difference of ≥ 10% in reoperation rate between the study groupsA statistically significant difference of ≥ 10% in severe complications rate between the study groupsA statistically significant difference of ≥ 20 *Quick*DASH points between the groups at any follow-up time-point

In case of termination of the study, participants that have already been recruited will complete follow-up. The study will end when all recruited participants have completed the follow-up, are excluded, or have otherwise withdrawn from the study.

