### Statistical analysis

For power and sample size calculations, the alpha value was set to 0.05. Our hypothesis is that CF will yield lower reoperation and complication rates, lower intra-operative radiation, and less intra-operative fluoroscopy time; thus, one-sided tests of proportions were used for sample size requirements calculations [47]. For all other variables, tests for non-inferiority were used with assumed means for ratio scalar and interval variables and assumed proportions for nominal variables [47].

Statistical power and sample size requirements for demonstrating clinically significant differences between the groups were calculated using minimal clinically important difference (MCID) values from the literature. Power and sample size data, including relevant assumptions for all calculations, are presented in Table 1.

We expect ≥ 80% power for reoperation rates, complication rates, severe complication rates, *Quick*DASH, SMFA, patient satisfaction, pain in motion and at rest, and ROM. However, we do not expect to achieve 80% power for analysis of grip strength, postoperative antibiotics use, secondary dislocation or nonunion rate, sick-leave time, fluoroscopy time, fluoroscopy DAP, or operation time (Table 1).

The minimal detectable differences (MDD) for various outcomes and study sizes are presented in Table 1. For some of the secondary and tertiary outcome measures, the MDD is smaller than the MCID meaning that the study is under-powered for proving non-inferiority between the groups. Early termination of the trial resulting in a smaller sample size would further reduce MDD, hampering the power of the study.

The final study groups consist of all participants that complete the follow-up and participants that withdraw but permit analysis; see the section “ Post-inclusion withdrawals and exclusions”. The study groups will be compared using the chi-squared test for categorical variables (reoperation, complication) and Student’s *t*-test for continuous variables.

Comparisons between the study groups will primarily be performed by “intention to treat” analyses. If large cross-over between study groups occurs, “as treated” analyses will be performed as well. Subgroup analysis stratified by Mayo classification, age, gender, open fracture, and high energy trauma is planned for all outcomes.

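### The stated 81% power for reoperation and the Discussion's account of early termination both leave out what the stopping rule does to the primary outcome: somewhat lower power, and an inflated difference after a stop

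*Protocol article*

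**What the plan says.** Four parts of the protocol article bear on this point.

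- **Sample size.** "Reoperation rates are assumed to be 13% for CF and 27% for TBW". On that basis, "The sample size of each arm needed to achieve 80% power is 98". The resulting 196 is then rounded up: "thus, we plan to recruit a total of 200 participants, yielding 81% power". No drop-out is expected for this outcome.
- **End of trial and early termination.** Interim analyses take place every six months from May 2024 and include everyone past the 6-week visit. Recruitment ends if the reoperation difference is statistically significant and at least 10%. Severe complications and QuickDASH have similar criteria. No adjusted significance level is stated. "In case of termination of the study, participants that have already been recruited will complete follow-up".
- **Statistical analysis.** For planning, "the alpha value was set to 0.05" and "one-sided tests of proportions were used for sample size requirements calculations". Final groups are compared by chi-squared test. This section also says that a smaller sample after early termination would hamper the power of the study in general.
- **Discussion.** Termination is attributed to large differences in reoperations, complications or QuickDASH, "which would negatively affect statistical power for analyses of other outcomes". The next sentence limits the loss to conclusions on those outcomes.

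**The concern.** The rule acts on the primary outcome itself. It stops recruitment when the interim reoperation difference happens to be large, in a sample well below 200 and with most follow-up still to come. The 36-month comparison then has two features that the protocol does not describe. It is smaller than the 200 on which the 81% rests, and its estimate is selected to be high, because the participants who produced the interim excess remain in the final data.

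At stake are the power that readers are told the trial has, and the size of the reoperation difference that it reports. The trial is meant to influence the choice of fixation, so an inflated difference would carry into practice.

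**Working it through.** **1. Inputs.** From the protocol: rates 13% and 27%; alpha 0.05, one-sided for planning; 1:1 allocation; 200 participants; recruitment from January 2023 at 50 per year; looks every six months from May 2024; a stop at p < 0.05 with a difference of at least 10 points; follow-up to 36 months; a final chi-squared test. Not given: when reoperations occur, and whether the interim tests are one-sided or two-sided. Both were varied.

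**2. The plan's own figure.** With z values 1.645 and 0.842:

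n per arm = (0.27×0.73 + 0.13×0.87) × (1.645 + 0.842)² / 0.14² = 0.3102 × 6.18 / 0.0196 ≈ 98.

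Power at 100 per arm = Φ(0.14/√(0.3102/100) − 1.645) = Φ(2.514 − 1.645) = Φ(0.869) ≈ 81%.

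The stated 98 and 81% are reproduced for one one-sided analysis of 200 participants. The two-sided equivalent is Φ(2.514 − 1.960) = Φ(0.554) ≈ 71% (70% with a pooled variance).

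**3. The looks.** May 2024 is month 16, and 200 participants are reached at month 48 (200/50 = 4 years). Six looks fall before then, at months 16, 22, 28, 34, 40 and 46. At the first, (16 − 1.4) × 50/12 ≈ 61 participants are past six weeks. The six looks have about 60, 85, 110, 135, 160 and 185.

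**4. What a smaller sample means.** An unselected comparison of 120 participants would have about 61% power one-sided and 48% two-sided. With a pooled rate of 20%, its standard error is √(2×0.20×0.80/60) = 0.073, so two-sided significance needs 1.96 × 0.073 = 14.3 points, about the true difference. Stopped trials reach significance at 36 months more often than this because their interim excess carries forward. That same carry-over inflates the estimate.

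**5. Simulation with the stopping rule.** Settings had 6,000 to 60,000 trials each. Recruitment was uniform, only the reoperation criterion was applied, and the timing shape was the same in both arms. Timing ran from all immediate to uniform over 36 months, with exponential and gamma shapes between. Everyone recruited by the stop was analysed at 36 months.

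| Result at 13% v 27% | Two-sided | One-sided |
|---|---|---|
| Trials stopping for reoperation | about 50–76% | about 53–84% |
| Mean 36-month difference after a stop (true 14) | 18.7–19.5 points (+34% to +39%) | about 18.3–18.8 points (+31% to +34%) |
| Stopped trials not significant at 36 months | about 12–21% | about 9–16% |
| Chance of a significant 36-month result | 64–70% | 73–79% |
| Same, fixed 200 participants | 70–71% | 80–81% |

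Mean recruitment at a stop was roughly 100 to 135.

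**6. Comparators for the overstatement.** A fixed 200-participant trial that ends significant also overstates: 16.7 points two-sided (16.7/14 = +19%) and 15.9 one-sided (15.9/14 = +14%), or about +13% to +20% across runs. Averaged over all trials under the rule, stopped or not, the overstatement is +7% to +19%.

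**7. Sensitivity (two-sided).** At 13% v 23%, 16–28% of stops are non-significant at 36 months and the overstatement after a stop is 65–75%. At 20% v 40% the figures are 9–13% and 20–22%. Adding a seventh look changes little (17.5–19% and +31% to +34%).

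**The case against.** The strongest reply is that the protocol already concedes the loss. The Statistical analysis section says that early termination hampers the power of the study without exempting the primary outcome, and Table 1 gives a minimal detectable difference for reoperation at n = 100 (0.2). Reoperation is also one of the other outcomes whenever QuickDASH or severe complications triggers the stop. This stands against one tempting reading: a reader might infer that the protocol says only other outcomes lose power, but it does not say so. What remains is that the concession is general and has no figure for this rule, the 81% ignores the rule, and overestimation is mentioned nowhere.

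Three further inferences go too far.

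- **That one stop in five is reversed.** This is the top of a 9–21% range. It needs a two-sided test and reoperations spread over many months, and the documents give no timing.
- **That such a trial contradicts its own stop.** A p value crossing 0.05 is not a contradiction. In at least 98% of these trials the 36-month difference still favours cerclage fixation, with a median of about 12–14 points two-sided. Nothing in the protocol makes the interim p value confirmatory.
- **That the rule adds a third to the estimate.** The third is conditional on stopping, and a significant fixed-size trial already overstates by about 13–20%.

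It can also be said that bias-adjusted estimation belongs in an analysis plan that is not shown. That is fair, and its absence is not the defect. The defect is in two statements that the protocol does make. Lastly, the Discussion's complications, where the rule says severe complications, is shorthand; the operative criterion is clear.

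**Conclusion.** The point holds as a matter of stated power and stated consequences. At the planning rates an early stop for reoperation is at least as likely as not. The chance of a significant 36-month result is then about 73–79% one-sided, not 81%, or 64–70% two-sided against 70–71% for a fixed 200. This loss is modest. The larger effect is on the estimate, about 18 to 19.5 points after a stop against a true 14.

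These figures assume steady recruitment of 50 per year, six unadjusted looks, the reoperation criterion alone, and reoperation timing between immediate and uniform over 36 months. They also depend on the true rates: the relative overstatement is larger if the true difference is smaller.

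**What to change.** Leave the recruitment rule unchanged for this point.

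1. In Sample size, restate the primary-outcome power as the power under the stopping rule, with the assumed reoperation timing and the sidedness of the test. In the Discussion, add that early stopping also lowers power and inflates the estimate for the outcome that triggers it.
2. Specify that, if recruitment stops early, the 36-month reoperation difference will be reported with a bias-adjusted estimate and interval that reflect the looks actually taken (for example median-unbiased or bootstrap-corrected), beside the unadjusted one.

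The cost is wording and a short simulation or bootstrap, with no added participants, visits or staff. The downside is a slightly less favourable stated power and, after an early stop, a smaller headline difference.

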## Trial status, timeline, and protocol amendments

The current protocol is the first version (1.1) of the protocol. Recruitment of participants began in January 2023. Based on statistics from previous years, we expect to recruit 50 subjects per year and thus recruitment is expected to end in 2027. The end of follow-up of the last recruited participant is expected to occur in 2030. No amendments have been made. In the case of future amendments to the protocol, the Swedish Ethical Review Authority will be informed and the ClinicalTrials.gov registry will be updated. Journals where study results or the protocol are published will be contacted, and a list of amendments will be included in future versions. Participant will be informed if affected by the amendment.

## Data Availability

This protocol can be accessed through open access by any party. Only the steering committee will have access to the final trial dataset. Anonymous group level data may be shared for non-commercial uses, if ethically sound, upon request to the authors.

## Abbreviations

WOW-OK: The With Or Without Olecranon K-wire
SPIRIT: Standard Protocol Items: Recommendations for Interventional Trials
TBW: Tension band wiring
CF: Cerclage fixation
*Quick*DASH: Shortened version of The Disabilities of Arm, Shoulder and Hand score
ISRCTN: International Standard Randomised Controlled Trial Number
RCT: Randomized controlled trial
SMFA: Short Musculoskeletal Function Assessment
bSMFA: Bother index in the SMFA
dSMFA: Disability index in the SMFA
VAS: Visual analogue scale
HAKIR: Swedish national quality register for hand surgery
ROM: Range of motion
DAP: Dose area product
MCID: Minimal clinically important difference
SD: Standard deviation
MDD: Minimal detectable difference
ICMJE: International Committee of Medical Journal Editors
